## Methods

### Study Design

This study combines the evaluation of the usability of the InCoPE-App with the effectiveness of the individualized exercise program concerning cognitive function, physical performance, and quality of life. Thus, a mixed methods design with different methodological components will be used. The evaluation of the usability and effectiveness of the InCoPE-App will be based on the use of the app for a duration of 18 weeks in a nursing home setting. This approach represents a field study and will be carried out as a cluster-randomized controlled trial in which the InCope-App will be used with people with dementia and the individualized, multidomain exercise program will be delivered by nursing assistants with the help of the app. The nursing homes will be cluster randomized, and each nursing assistant will subsequently recruit at least 2 people with dementia (see Figure 1).

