### Participants

To evaluate the InCoPE-App in terms of usability and effectiveness, 2 different study samples are required (see Figure 1). The first sample will include the future users of the InCoPE-App (ie, nursing assistants). To this end, initial contact will be established through the heads of care facilities in southwestern Germany who suggest potentially interested nursing assistants, who will subsequently receive detailed information about the aims and the content of the study. The following inclusion criteria must be fulfilled: (1) willingness to participate in the training to familiarize themselves with the InCoPE app, (2) command of the German language as the InCoPE-App is only available in German at this time, and (3) employment at the nursing home for at least 18 weeks. External employees (eg, physical therapists) will be excluded.

The second sample will include participants with primary dementia living in nursing homes. This sample will be drawn to evaluate usability and trends toward the effectiveness of the individualized exercise program as delivered by the InCoPE app. Participants in the second sample will be selected by nursing assistants. Before entering the study, written consent by participants or their legal guardians will be obtained. Prior to the intervention, a clearance certificate from the participant’s general practitioner will be collected, which will also include information about the dementia diagnosis and other pertinent information such as medication intake and comorbidities. Additional inclusion criteria are (1) Alzheimer disease, vascular dementia, or other primary dementia; (2) mild to moderate stage of dementia (Mini-Mental State Examination [MMSE]: 10-24); (3) age older than 65 years; and (4) walking ability of at least 10 meters with or without a walking aid. Exclusion criteria include (1) secondary dementia, (2) other severe cognitive impairments, (3) other severe neurological conditions, (4) other severe acute diseases, and (5) severe motor impairments.

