### Intervention

The individualized exercise program for people with dementia is based on earlier work by this research group and includes a combination of cognitive and physical exercises [19]. The included exercises were further differentiated to ensure a higher degree of individualization following the idea of individualized medicine [20]. The individualized exercise program is embedded in the InCoPE-App, which will be utilized by nursing assistants. The InCoPE-App will be installed on a tablet device (Android), and nursing assistants will be trained in the appropriate use of the app in order to test and instruct people with dementia. The training comprises theoretical online modules for self-study (eg, theoretical basics of physical exercise with people with dementia, objective testing of physical and cognitive performance in people with dementia, first steps with the InCoPE-App) and 2 face-to-face meetings (between project members or research staff and nursing assistants) for the usage of the InCoPE-App. The InCoPE-App contains detailed photographic materials and descriptions to offer visual support in the execution of the proposed tests and exercises.

The tests assessing motor and cognitive performance included in the InCoPE-App are based on published recommendations and were used with people with dementia before [21,22]. On the basis of cluster analysis in a large sample of people with dementia who participated in our group’s previous randomized controlled trial [19], we identified 4 homogeneous subgroups of people with dementia [23] who were also considered when we designed the InCoPE-App: participants with (1) below-average motor and cognitive performance, (2) average cognitive performance and above-average motor performance, (3) above-average cognitive and motor performance, and (4) above-average cognitive performance and below-average motor performance. The initial testing of physical and cognitive performance included in the InCoPE-App will be used to determine whether an individual belongs to cluster 1, 2, 3, or 4. Testing will be repeated every 3 weeks during the 18-week intervention period to allow the InCoPE-App to regularly adjust the duration, intensity, and contents of the cognitive and physical exercises based on the individual’s needs. We anticipate that the desired physical and cognitive adaptation to the exercise program will be achieved by gradually increasing exercise difficulty and intensity (eg, number of repetitions).

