Each nursing assistant will use the app to deliver the individualized exercise program within the 18-week intervention to 2 people with dementia. The overall usability will be assessed after the intervention using the Post-Study System Usability Questionnaire (PSSUQ) [24]. The PSSUQ gives insight into user satisfaction with a system (eg, system usefulness, information quality, and interface quality). This questionnaire can be considered a useful tool for field studies [24]. We will use PSSUQ version 3, which is comprised of 19 items such as system usefulness, information quality, and interface quality rated on a 7-point Likert scale (1: strongly agree to 7: strongly disagree) [24,34]. Furthermore, usability will be assessed using the ISONORM questionnaire [25], which covers the implementation of the 7 defined criteria based on the International Ergonomics Standard DIN EN ISO 9241-110. This questionnaire operationalizes the 7 criteria of the EN ISO 9241-10 and was developed to evaluate software development [35]. The completion of the questionnaire takes 10 minutes, and bipolar statements from 35 items are assessed using a 7-point Likert scale (1: very negative to 7: very positive) [35]. The perceived hedonic and pragmatic quality of the InCoPE-App will be assessed using the AttrakDiff 2 questionnaire [26]. This questionnaire evaluates the participants’ perceptions of the InCoPE-App by means of semantic differentials.

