The Timed Up & Go (TUG) test will be conducted by asking participants to rise from a chair, walk 3 meters, turn around, and then go back and sit down again on the chair [30]. Nursing assistants will instruct participants while using the InCoPE-App to assess the time taken by each participant. Time is measured from the initial impulse to stand up until participants are seated again. Everyday walking aids are allowed. For the 6-meter walk test (6MWT) [31], participants will be asked to walk from one side of the room to the other side, where the distance of 6 meters will be marked using start and finish lines on the floor. When participants cross these lines, the time required to walk 6 meters will be measured using the InCoPE-App. In front of the starting line and behind the finish line, participants will have about 2 meters for acceleration and deceleration. If needed, participants are allowed to use their walking aids. Strength and function of lower limbs will be assessed using the modified 30-second chair stand test (30s CST). For the modified 30s CST, participants will be asked to stand up from a chair (height 46 centimeters, with armrests) as often as possible for 30 seconds. The modified version allows the use of armrests [32], which is essential for the majority of older adults with dementia to safely perform this test. While testing lower extremities, no walking aids are allowed. Static balance will be determined using the Frailty and Injuries: Cooperative Studies of Intervention Techniques- subtest 4 (FICSIT-4) [33], in which participants are asked to perform 4 different standing positions (Romberg, semitandem, tandem, and single leg) for 10 seconds without walking aids or other assistance. The FICSIT-4 performance is rated on a scale of 0 to 5 points. If participants cannot hold the first position for at least 3 seconds, a score of 0 is given. In contrast, participants receive a score of 5 if they are able to stand in the most difficult (ie, single leg) position for at least 10 seconds.

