### Randomization and Concealment

The residents with dementia recruited by nursing assistants will be allocated to either the CG or IG. This allocation will be performed by cluster randomization as it is not possible to blind participants, nursing assistants, or study personnel regarding group allocation. Participants in the CG will only receive conventional treatment such as individualized medication, standard care, or therapeutic applications for 18 weeks. Participants in the IG will receive the individualized exercise program in addition to conventional treatment. To ensure equal conventional treatment for the IG and CG during the intervention, it will be continuously documented.

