### Strength and Limitations

Through the innovative and timely development method and thorough evaluation and integration of users’ experiences [49], we expect an application that is highly usable and feasible in everyday care situations. The acceptance of the InCoPE-App will promote its regular usage and thus allow testing and training residents with dementia individually. The regular conduct of physical and cognitive tests that is implemented as an essential part of the app will help to document the progression of disease symptoms and can thus be regarded as an additional objective tool for clinical documentation, which is required on a regular basis in a nursing home setting. The individualization of the exercise program, which has been described as critically important in previous research [9,20], is the key innovative and novel component of the InCoPE-App.

It is unlikely but possible that usability of the InCoPE-App will be rated as low by nursing assistants. In this case, fundamental changes within the application will be required to increase acceptance and practicability, which may have a considerable impact on the effectiveness of the exercise program. There are risks from a technical point of view that might impede the usability of the InCoPE-App, such as possible failure of the tablets to store the data on each tablet. To lower this risk, we will provide the required tablet with the installed InCoPE-App for each participating nursing home. In addition, nursing assistants can contact the research team to report technical issues and get help at any time.

Another limitation is the rather small number of participating people with dementia. This sample size is sufficient to detect moderate within and between interactions. However, it might be too small to statistically detect small effects. The use of the InCoPE-App within everyday life allows us to gain information about everyday feasibility and suitability; thus, results can be more easily transferred to daily routine. 

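### The article places the app, its training and, read literally, program delivery in all homes, yet reserves the program for the intervention arm; no restriction in control homes is stated, so the contrast can be diluted

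*Protocol article*

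**What the plan says.** Randomization is by home (Study Design): "The nursing homes will be cluster randomized, and each nursing assistant will subsequently recruit at least 2 people with dementia". The control condition is set under Randomization and Concealment: "Participants in the CG will only receive conventional treatment such as individualized medication, standard care, or therapeutic applications for 18 weeks". The same section gives the exercise program to the intervention group (IG) on top of conventional treatment, and has conventional treatment documented throughout.

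Other sections describe the app, its training and its use without separating the arms:

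- **Tablet** (Strength and Limitations): "we will provide the required tablet with the installed InCoPE-App for each participating nursing home".
- **Entry criterion for all nursing assistants** (Participants): "willingness to participate in the training to familiarize themselves with the InCoPE app".
- **Training** (Intervention): "nursing assistants will be trained in the appropriate use of the app in order to test and instruct people with dementia". The online modules include "theoretical basics of physical exercise with people with dementia", and two face-to-face meetings follow.
- **Delivery** (Primary Outcomes): "Each nursing assistant will use the app to deliver the individualized exercise program within the 18-week intervention to 2 people with dementia".
- **Numbers** (Sample Size): 22 assistants with 2 residents each; the resulting 44 residents are 22 IG plus 22 control.
- **Abstract, Methods**: assistants test 44 residents with the app every 3 weeks and apply the program.
- **Patient Documentation**: the residents whom assistants train get an ID whose first digit shows IG or control.

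Table 1 marks MMSE, digit span, TUG, 6-meter walk, chair stand and FICSIT-4 as implemented in the app; only the QOL-AD is not. For the TUG, "Nursing assistants will instruct participants while using the InCoPE-App to assess the time taken by each participant". Under Intervention, the initial test in the app assigns the resident to one of four performance clusters, and the cluster determines the exercise content.

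**The concern.** The trial compares the program plus conventional treatment with conventional treatment alone, so it needs the program to stay out of the control arm. If control homes need the app for the pre and post tests, they hold the tool that turns those test results into an exercise plan. If their assistants also take the training, they know how to deliver it. The article presents the app as usable without prior exercise experience, and staff are not blinded, so little stands in the way of use.

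Any program use with control residents moves the control arm toward the intervention arm and shrinks the group-by-time effect. A program that works could then look weaker than it is, in a trial whose authors already call the sample rather small.

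The same unclear wording affects a second primary objective. The usability sample counts all 22 assistants as app users, which does not fit a control arm that gets conventional treatment only.

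**Working it through.** **1. The passages side by side.** With 22 assistants and 2 residents each, 22 × 2 = 44, which is IG 22 + control 22. If every assistant delivers the program to 2 residents, all 44 receive it and no untreated control remains. Randomization and Concealment rules that out, so the passages cannot all be read literally. No section says that the exercise module is withheld in control homes, that training there is limited or postponed, or that program use there is monitored.

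**2. The plan's usability figure.** Inputs from Sample Size: problem probability 0.1, 22 assistants. The chance of seeing a problem at least once is 1-(1-0.1)^n.

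- n = 22: 1-0.9^22 = 0.9015. The stated 90% is reproduced.
- With 22 control residents at 2 per assistant, 22/2 = 11 assistants belong to control homes and 11 to intervention homes.
- n = 11: 1-0.9^11 = 0.686.

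The 90% therefore needs all 22 assistants as users. If only intervention assistants use the exercise part, the chance for problems in that part is about 0.69. Study Design allows more than 2 residents per assistant, so 11 is approximate.

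**3. The plan's resident sample size.** Inputs from Sample Size: partial eta squared 0.07, alpha 0.05, power 0.95, repeated-measures ANOVA with within-between interaction. Two groups and two time points (pre, post) follow from the design. The correlation between repeated measures is not stated; 0.5 is assumed.

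- f = √(0.07/0.93) = 0.2744.
- Noncentrality λ = f² × N × m/(1-ρ) = 0.07527 × 44 × 2/0.5 = 13.25, with 1 and 42 degrees of freedom.
- Power at N=44 is 0.945, and 0.95 is reached at N=46. The stated 44 is reproduced to within 2 participants.
- The result depends on the assumed correlation: power at N=44 is 0.85 at ρ=0.3 and 0.98 at ρ=0.6.

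**4. Effect of control-arm uptake.** The article gives no contamination rate, so c is an assumption: the share of the program effect that reaches the control arm on average. The observed difference is (1-c) × the true difference, so f becomes (1-c) × 0.2744. Clustering is ignored, and ρ=0.5 is kept.

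| c (assumed) | f | Power at N=44 | N for 0.95 |
|---|---|---|---|
| 0 | 0.2744 | 0.945 | 46 |
| 0.10 | 0.2469 | 0.893 | 56 |
| 0.25 | 0.2058 | 0.760 | 80 |
| 0.50 | 0.1372 | 0.428 | 176 |

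For scale, one control assistant delivering the full program to both of their residents would affect 2/22 = 9% of the arm.

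**The case against.** A reader might infer that control homes do receive the app, that their assistants must take the training from the start, and that the contrast is therefore diluted. The document does not support that reading:

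- The tablet sentence stands in a paragraph on technical risk and may loosely mean homes that use the app.
- The training criterion is willingness, not attendance, and no section dates the training in control homes.
- Randomization and Concealment states the arm rule, and no section gives control residents the program explicitly.
- The participant flow figure is not shown, and a condensed article may leave app configuration to the full protocol.
- Full contamination would take effort: two 60-minute sessions a week for 18 weeks is 36 sessions, by staff whose workload had grown. Theory modules alone would not carry the full effect.
- A reader might add that the purpose of randomizing homes is lost. The only reason the article gives for cluster randomization is that blinding is impossible.

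These points stand, and they make dilution a risk of unknown size. They do not remove the conflict. The problem is not an omitted detail: several sections make statements that cover all assistants or all homes and cannot be squared with the control condition. Documenting conventional treatment records co-treatment; it neither prevents nor mentions use of the app's exercises. The app does log completed training sessions (Table 2), which is a useful record. However, it is offline and its data are transferred only after the 18 weeks, so program use could not be seen remotely in time to correct it.

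A further objection is that restricting control homes would leave too few usability raters. Under the stated control condition, control assistants would not use the exercise part anyway. The fall from 0.90 to 0.69 is thus an inconsistency already in the plan, not a cost of the fix.

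**Conclusion.** The concern holds as an internal conflict with a plausible consequence. The article assigns app, training and, read literally, delivery to all assistants in all homes, while control residents are to receive conventional treatment only. That control homes hold the full app is a reasonable inference from the in-app testing and the unrestricted wording; it is not stated outright. The contrast can be diluted, and by how much cannot be known from the document. The power figures for c of 0.10 to 0.50 illustrate assumed uptake, with an assumed correlation of 0.5 and no allowance for clustering. The usability result needs no contamination assumption: with about 11 full-app users the discovery chance is 0.69, given 2 residents per assistant.

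**What to change.** 1. **Reconcile the text by arm.** In the Abstract, Participants, Intervention, Primary Outcomes, Sample Size, Patient Documentation and Strength and Limitations sections, state which homes have the app, which functions are active and when, and who delivers the program, consistently with Randomization and Concealment.
2. **Limit the app in control homes.** For the 18 weeks enable only the test functions there, with the cluster result and the exercise module hidden.
3. **Stage the training.** Before the pre-test, train control assistants in testing only. Give the exercise modules and the exercise part of the meetings after post-assessment; the Dissemination section already lets participating homes go on using the app after the evaluation.
4. **Report uptake.** Use the existing log of completed training sessions on control tablets to report any program use in the control arm.
5. **Restate the usability basis.** Say how many assistants use the full app. If it is about 11, give 0.69 as the discovery chance for the exercise part; the 0.90 could then apply only to functions that all 22 use.

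The cost is a second app configuration and a later training contact in control homes. The log check needs no new data collection.

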### Dissemination

A manuscript with the results on usability and effectiveness based on the primary outcomes will be published in a peer-reviewed journal. Additional manuscripts focusing on the secondary outcomes of the InCoPE-App will be prepared and submitted for publication in peer-reviewed journals. Upon completion of the study and after publication of the primary manuscript, all anonymized and summarized data can be requested from the researchers at the Institute of Sports and Sports Science of the Karlsruhe Institute of Technology, Germany.

The InCoPE-App will be evaluated in this study with respect to usability and effectiveness. After this evaluation, the participating nursing homes are allowed to further use the app to train their residents with dementia. Based on this, a dissemination plan will be developed to provide more nursing homes with the app, which is highly relevant in 2 ways. First, the continuing pandemic requires nursing assistants and residents with dementia to abide by strict hygiene measures, which is difficult when conducting a group-based exercise program possibly delivered by external employees such as trainers or instructors. Second, apart from pandemic circumstances, individualized group exercise programs in nursing homes are often delivered by nursing assistants who are not sufficiently trained for this purpose. Thus, the overall effect of exercise programs in nursing home settings is often limited. The InCoPE-App addresses this gap as it enables nursing assistants to deliver a scientifically based and individually assigned exercise program to people with dementia without requiring exercise science expertise or excessive prior training. Implementing the app in a nursing home setting may also be associated with economic advantages as additional employees with exercise science background to carry out a dementia-specific individualized exercise program may not need to be hired. One can conclude that the additional temporal expense might be balanced and the benefit of each participant can outweigh the expenses. The exact time and personnel resources required for implementation of the InCoPE-App will be assessed in the context of this study. This information can be used as key data to establish the InCoPE-App in other nursing homes.

### Conclusion

The InCoPE-App is a novel, innovative, tablet-based intervention that allows nursing assistants to individually test and train people with dementia with regard to physical and cognitive capacities while meeting the hygiene and safety measures in place during the current COVID-19 pandemic. The InCoPE-App can be used by nursing assistants without prior exercise experience as it provides low-threshold testing procedures and implementation of an exercise program without the need for expert knowledge. This fact is also relevant in times after the pandemic constraints, because supplementation of the traditional treatments with the best possible physical exercise program is always challenging for nursing assistants who do not have the special training to deliver an individualized exercise program. The InCoPE-App will allow nursing assistants to regularly test the physical and cognitive performance of each individual and to subsequently train people with dementia on that basis. To the best of our knowledge, there is currently no app available that applies a similar approach in a nursing home setting. The InCoPE app is expected to provide nursing assistants a means to provide their residents with dementia a usable and feasible individualized exercise program that may increase physical and cognitive performance as well as quality of life. This may in turn have a positive impact on disease progression and nursing care.

